## Abstract

Postpartum depression (PPD) is a complex combination of physiological, emotional, and behavioral alterations associated with postpartum chemical, social, and psychological variations. It does harm to the relationship between family members that could potentially last for years. However, standard depression treatments are not ideal for PPD, and the outcomes of these treatments are debatable. Transcranial direct current stimulation (tDCS) is an emerging technology that could provide patients with PPD with a safe and non-pharmacological treatment. tDCS can relieve depression by directly stimulating the prefrontal cortex through the excitatory effect of the anode. It may also ease depression indirectly by promoting the production and release of the neurotransmitter GABA. The mechanism of tDCS makes it an ideal therapeutic approach to treat PPD, although it has not been widely used, and its effect has not been evaluated systematically and effectively. A double-blind, randomized controlled trial will be conducted involving 240 tDCS-naive patients with PPD, who will be randomly divided into two groups. One group will receive routine clinical treatment and care with active tDCS, and the other group will receive routine clinical treatment and care with sham tDCS. Each group of patients will receive a 3-week intervention during which they will receive 20 min of active or sham tDCS 6 days per week. The Montgomery–Åsberg Depression Rating Scale will be administered before the intervention as a baseline and on each weekend throughout the intervention phase. Before and after the intervention, the Perceived Stress Scale and the Positive and Negative Affect Schedule will be evaluated. Side effects and abnormal reactions will be recorded during each treatment. As antidepressants are banned in the study, the results will not be affected by drugs and will therefore be more accurate. Nonetheless, this experiment will be conducted in a single center as a small sample experiment. Therefore, future studies are required to confirm the effectiveness of tDCS in treating PPD.

## 1. Introduction

Postpartum depression (PPD) is a complex combination of physiological, emotional, and behavioral alterations associated with postpartum chemical, social, and psychological variations (Wang et al., 2021). The postpartum period begins after childbirth and lasts up to 12 months after the delivery. PPD can result in significant financial losses annually. Globally, 67% of financial resources are directly allocated to psychiatric health services. A recent review suggested that the global prevalence of PPD was approximately 17% (Wang et al., 2021). This prevalence level means that PPD may significantly affect the wellbeing of parents, the relationship between mothers and their children, cognitive development, social abilities, and behavioral outcomes among children (Nilova et al., 2017). The high incidence rate of maternal mental health disorders presents a risk not only to mothers but also to children and other associated family members. People who are married and suffer from PPD are more likely to separate and divorce, mistreat and neglect their children, experience chronic mental disorders, die by suicide, and commit infanticide (Wisner et al., 2006; Field, 2011; Beestin et al., 2014; Stein et al., 2014; The American College of Obstetricians Gynecologists Committee Opinion no. 630., 2015; Punescu et al., 2017). Numerous studies (Cheng et al., 2016; Closa-Monasterolo et al., 2017; Koutra et al., 2017; Van der Waerden et al., 2017) show that PPD results in decreased cognitive function and increased behavioral problems among infants and children. If left untreated, the manifestations of PPD can last for years. It has been calculated that approximately 30% of women suffer from PPD in the community, with the percentage rising to 50% in clinical settings (Goodman, 2004; Vliegen et al., 2014). Therefore, the appropriate treatment of PPD is crucial to ensuring harmony among families and enhancing the relationship between mother and child.

The treatment of depression typically relies on psychotherapeutic methods, such as cognitive-behavioral therapy (CBT), interpersonal psychotherapy (IPT), and social psychotherapy, which can be combined with antidepressants, such as tricyclic antidepressants or selective 5-hydroxytryptamine reuptake inhibitors. Nevertheless, it remains controversial whether the conventional treatment approaches for PPD are effective based on the effects of the treatment approaches mentioned above (Orsolini and Bellantuono, 2015; Uguz, 2016; Thomson and Sharma, 2017). It takes time for psychotherapy to be effective, and it is generally ineffective in cases of major depression. Furthermore, barriers to participation in psychotherapy include perceived stigmatization, the lack of trained therapists specializing in IPT or CBT, the investment of time necessary, as well as the need to arrange childcare needs and its associated costs (Li et al., 2020). While antidepressants may be effective within a few weeks, the increased risk of adverse consequences in children due to fetal exposure has led mothers to refuse to use them while nursing (Sorenson, 1990). However, antidepressants are clinically appropriate for women with severe mental disorders during pregnancy and postpartum, when there are significant risks to the mother, fetus, or baby (Howard et al., 2014). Individuals with PPD may experience increased levels of anxiety when starting an antidepressant-based treatment approach, with previous studies showing that such patients consistently deny medication or are forced to continue with low doses (Boath et al., 2004; Guille et al., 2013). Therefore, the low acceptability of existing treatment approaches may result in the inadequate treatment of depression in this group. Regarding long-term treatment options, it is imperative to explore effective alternatives to treating PPD without adverse side effects. Currently, such alternatives remain inadequate.

Non-invasive brain stimulation (NIBS) is a non-traumatic, convenient, safe, and effective brain function therapy technique widely used in clinics. As a typical NIBS approach, transcranial direct current stimulation (tDCS) may be an effective brain stimulation medical technique with the potential to be an “optimal” treatment method for PPD. Additionally, tDCS, a local brain stimulation-based treatment approach, is dependent on the presence of abnormalities in the activity of the frontal lobe region of the brain, particularly the left and right dorsolateral prefrontal cortex (PFC) (George et al., 1997; Speer et al., 2000; Fitzgerald et al., 2003; Ardolino et al., 2005). In a meta-analysis of 10 studies, researchers found that, compared to sham tDCS, active tDCS was more favorable in alleviating symptoms of depression after 2 to 3 weeks of treatment (Kalu et al., 2012). Significantly, tDCS has proven to be safe in a wide range of trials. In one study involving the side effects of tDCS, 77 healthy controls and 25 patients with neurological diseases were examined 567 times, with the most prevalent side effects involving slight tingling, moderate fatigue, and mild tickling under the stimulation electrodes. After tDCS, approximately 10% of headaches and <3% of instances of insomnia and nausea were reported (Poreisz et al., 2007). Additionally, tDCS is an available treatment approach. The instrumentation required is cheap and mobile, and tDCS can be administered by trained technicians or by the individual themselves.

In summary, tDCS is a novel, safe, and non-pharmacological treatment technique for individuals suffering from PPD. The purpose of this protocol is to evaluate the efficacy and safety of tDCS as a method of treating PPD with a forward-looking, double-armed, sham-control, randomized controlled trial (RCT) protocol toP. This may be a guide to a larger multi-centered RCT that explicitly values the therapeutic effects of tDCS on the treatment of PPD. This study protocol may also be used to derive the initial impact dimensions for the sample size required to complete the most complete and reliable RCT.

## 2. Method

### 2.1. Study design

The RCT will involve recruiting patients with PPD for up to 1–2 years from professional postpartum psychological health projects in the Departments of Psychosomatic Medicine, Rehabilitation Medicine, Obstetrics, and Gynecology at the First Affiliated Hospital of Nanchang University. To recruit enough participants, leaflets and posters will be posted at the place of recruitment, and physicians will be informed about this study to assist in identifying qualified participants. The research coordinator conducted a baseline visit before the start of the active study to collect information on baseline demographics, to gain access to health services, and to gather baseline Montgomery-Asberg Depression Rating Scale (MADRS) measures.

In addition to the intervention, sham control will also be carried out within the Core Clinical Experiment at the first Affiliated Hospital of Nanchang University by well-trained researchers to guarantee proper supervision throughout the procedures. The active period of the experiment involving altogether 18 intervention or sham control sessions lasting for 20 min for approximately 3 weeks (6 days per week). The researchers who manage the session will record the date of every visit, the participant's blood pressure and heart rate, the starting and finishing times of sham tDCS, and interruptions, if any. All confounding factors (such as a previous history of depression, treatments, family history, etc.) will be analyzed. Outcome questionnaires will be collected from patients with PPD at three time points: before the procedures after enrollment (T1), 1 week after completing the procedures (T2), and 3 weeks after completing the procedures (T3). Follow-up questionnaires will be completed in person or by phone 8 weeks after completing the procedures. Patients will receive email updates concerning enrollment goals and the integrity of follow-up to help them to perceive the contributions that they made while participating in the study. Participants are then contacted with outcome information gathered and organized by professionally trained and experienced researchers. Personal outcome information is blind to the researchers, participants, and physicians who provided clinical treatment and care in the study group assignment.

The flow diagram of this study design is shown in Figure 1, and the evaluation of different time points is shown in Table 1.

**Figure 1 F1:**
[figure not shown]
A flow diagram of the trial design. First, eligible patients with PPD are recruited and a baseline assessment is conducted. Then, patients are divided into the intervention and control groups (active tDCS or sham tDCS) randomly and research is implemented for 3 weeks, and outcomes are recorded timely. Finally, patients are followed up for 8 weeks for statistical analysis.

**Table 1 T1:** Data on the design of the study.

**Point in time**		**Screening stage**	**Treatment period 1 (week 1)**	**Treatment period 2 (week 2)**	**Treatment period 3 (week 3)**	**Follow-up (8 weeks)**
	Informed consent	×				
Enrolment	Inclusion and exclusion criteria	×				
	Basic information	×				
	Past medical history	×				
	Withdrawal, drop out, and termination criteria		×	×	×	×
Intervention	Therapeutic parameter record		×	×	×	×
Assessment	Montgomery-Åsberg Depression Rating Scale (MADRS)	×	×	×	×	×
	Perceived Stress Scale (PSS)	×	×	×	×	×
	Positive and Negative Affect Schedule (PANAS)	×	×	×	×	×
	Overall efficacy evaluation		×	×	×	×
	Complications		×	×	×	×
	Adverse events recorded		×	×	×	×

Corresponding assessments are recorded at five different time points.

### 2.2. Participants and recruitment

Potentially eligible participants will be recruited through the Internet, leaflets, and posters, and preliminary screening will be conducted by trained psychologists, rehabilitation physicians, and obstetricians or gynecologists on visits to the First Affiliated Hospital of Nanchang University. The researchers will then conduct further screening based on eligibility and exclusion criteria to identify eligible participants. Finally, all the participants will provide written informed consent.

### 2.3. Eligibility criteria

To be included in the study, the participants must meet the following criteria:

(1) Be postpartum and at least 18 years old;

(2) Satisfy the current criteria for the diagnosis of severe depression or at least a severe depression paroxysm of moderate severity based on the fifth edition of the Diagnostic and Statistical Manual of Mental Disorders (DSM-5);

(3) Have been provided with and have refused to take antidepressants prescribed by their attending clinicians at the recruitment location;

(4) Be evaluated to qualify for outpatient psychiatric treatment by a chief researcher; and

(5) Have never received tDCS but agree to this treatment approach and comprehend the interpretations of the study and the associated questionnaires.

### 2.4. Exclusion criteria

Participants will be excluded from the study if they

(1) Fail to meet the criteria for the diagnosis of severe depression or the severe depression paroxysm of less than moderate severity at the time of the study;

(2) Have been diagnosed with alcohol or substance use disorder by the DSM-5 within the last 6 months;

(3) Have severe and active medical or neurologic disorders or a history of epilepsy;

(4) Are taking carbamazepine (because it might reduce the effectiveness of tDCS therapy), benzodiazepines, or other anticonvulsants daily at the time of the study;

(5) Have metal objects into the skull, electrically transplanted into the body, or transplanted to the scalp to stimulate the skin at the skin defect; and

(6) Have serious physical diseases or complications cause the patients can't endure the tDCS stimulation.

### 2.5. Sample size

The sample size involved in this study will be based on that of previous studies. The improvements will be evaluated using identical sample sizes based on the following estimated formula:

$\eta =\frac{2\bar{pq}{\left(Z_{\alpha }+Z_{\beta }\right)}^{2}}{{\left(p_{1}-p_{2}\right)}^{2}}$. The first type of error is 5% (α = 0.05) and 90% power (β = 0.10), and the estimated sample size requires 79 participants per group. Given the high drop-out rate (~15–20%) in the study (Lever Taylor et al., 2016), at least 198 participants will be required to achieve the target of 79 participants in each group. We receive approximately 200 patients with PPD per month, combined with approximately 120 patients suffering from moderate to major depressive disorders. According to the recruitment approach of a previous study (Walton et al., 2014), we estimate that 60 patients (50%) may be ineligible owing to antidepressant-based treatment 15 patients may be ineligible for various reasons such as having severe physical diseases or complications, and 20 patients within the remaining 45 patients (50%) may agree to participate in the preliminary study. Therefore, the enlisting of 240 patients suffering from PPD could be achieved within a year.

### 2.6. Randomization and allocation concealment

Following the informed consent process and the assortment of baseline information, individuals suffering from PPD who meet the eligibility criteria pertinent to this study will randomly receive active or sham tDCS. A study aide outside the confines of this study will present an assignment sequence using a randomized table of arranged blocks, and group distributions will be put into air-tight envelopes. The randomization identification numbers (RIDs) in the table will be stratified by the age of the newborn baby at enrollment to balance the gestational age of each group. Therefore, the first layer of RIDs will be distributed to participants who are <3 weeks into the postpartum period at the time of registration. The second layer of RIDs will be distributed to participants who are 3 weeks or more into the postpartum period. The experiment coordinator, while remaining blind to the group assignments, will select an envelope to include in the participants' chart. The experimenter will then open the envelope to ascertain the packet assignment, and program the tDCS device accordingly. The researchers will document the outcome measures objectively. The participants and researchers collecting maternal and infant clinical outcome data will also remain blind to the group distributions.

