### 2.7. Blinding

As this will be a double-blind study, a third party not involved in the experiment will administer and supervise the blind strategies as follows:

(1) Participants will not be permitted to open the envelopes in the order in which they will be involved in the study. Assuming a tDCS model of modes A and B, the study implementer will not have any knowledge of what the stimuli represented.

(2) The A model represents an active stimulus, and the B model represents a sham stimulus. A third-party evaluator will evaluate the treatment results without information regarding the subgroup.

(3) The first non-blind method will be conducted until the applied mathematical analysis is completed to overcome subjective tendencies among the analysts during the data analysis process. After statistical analysis, a second non-blinded test will be conducted to determine the intervention group.

(4) Participants will be randomly asked whether they received an active or sham stimulus to ensure that they do not recognize the stimulation pattern.

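### Section 2.6 lets the experimenter learn the assignment, while 2.7 says the implementer cannot know it and then prints the key; operator blinding is contradictory as written if the two are one person

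*Protocol article*

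**What the plan says.** Section 2.6 describes the allocation route. A study aide from outside the trial prepares the blocked sequence, and "group distributions will be put into air-tight envelopes". Next, "The experiment coordinator, while remaining blind to the group assignments, will select an envelope" for the participant's chart. After that, "The experimenter will then open the envelope to ascertain the packet assignment, and program the tDCS device accordingly". The section names the people who stay blind: the coordinator, as just quoted, and then "The participants and researchers collecting maternal and infant clinical outcome data will also remain blind to the group distributions". The experimenter is on neither list.

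Section 2.7 calls the study double-blind and puts a third party from outside the experiment in charge of the blinding. Item (1) supposes two device modes, A and B, and says "the study implementer will not have any knowledge of what the stimuli represented". Item (2) begins: "The A model represents an active stimulus, and the B model represents a sham stimulus". The same item adds: "A third-party evaluator will evaluate the treatment results without information regarding the subgroup". Item (3) sets out a two-step unblinding in which the intervention group is identified only once the statistical analysis is complete.

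Two other places bear on this. Section 2.11 says the participating therapists carry out assessments as well as treatment. Section 2.11.2 has a designated therapist give the sessions, without saying whether this is the person who opened the envelope.

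**The concern.** The two sections give incompatible accounts of what the person setting the device knows. In 2.6 that person finds out the assignment; in 2.7(1) the person implementing the study does not know what the modes mean. A letter code could have reconciled them, but the next item of 2.7 discloses the code in the document that staff work from.

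The primary outcome is the MADRS (section 3.1), and the Discussion accepts that subjective factors can significantly influence the scales used. The design has 18 sessions per participant (section 2.1). If anyone who treats or rates knows the arm, expectation can reach the score, and analysis cannot remove that bias afterwards. There are only two modes, so the printed key decodes both arms at once.

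**Working it through.** This is a question of procedure, so no arithmetic applies. The check sets the statements side by side and follows each reading through.

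**Inputs**
- 2.6: the envelope holds the group allocation; no coded label is mentioned.
- 2.6: the experimenter opens it, learns the assignment and programs the device.
- 2.6: coordinator, participants and outcome collectors are blind; the experimenter is not listed.
- 2.7(1): the implementer does not know what A and B represent.
- 2.7(2): A is active, B is sham; a third-party evaluator lacks group information.
- 2.7(3): the intervention group is identified after the analysis.
- 2.11 and 2.11.2: therapists conduct assessments; a designated therapist gives the sessions.

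**Operator**
1. Experimenter and implementer are the same person, and the envelope names the arm (the plain reading of 2.6). The operator knows the arm on opening it, so 2.7(1) is false.
2. Same person, but the envelope holds only A or B. The key in 2.7(2) decodes the letter for anyone who has read the protocol. 2.7(1) again fails in practice.
3. Different people: one unblinded person sets the device and a separate blinded person gives the sessions. 2.7(1) can then be true of the second person, provided the device does not show that person a mode letter that the printed key would decode. The article does not describe this arrangement.

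**Analyst**
4. The analysis groups are labelled A and B as on the device. The printed key then leaves the second unblinding step in 2.7(3) with nothing to reveal.
5. The analysis groups carry separate labels. The key tells the analyst nothing, and 2.7(3) can stand.

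The article does not say whether 4 or 5 applies.

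**Rater**
6. 2.6 and 2.7(2) both state that outcome assessment is blind, and nothing in the envelope procedure directly cancels that. However, 2.11 gives assessments to the therapists, while 2.7(2) gives evaluation to a third party. If a therapist both programs the device and rates, the operator's knowledge reaches the primary outcome. The text neither says nor excludes this.

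**The case against.** The best defence is that the article never equates the experimenter, the study implementer and the designated therapist. One unblinded person setting the device while others treat and rate is a recognised arrangement in sham-controlled trials, and leaving the experimenter off the blind list in 2.6 fits it. On that view the defect may be only loose wording in 2.7(1). Also, 2.7(1) introduces modes A and B as a supposition, so the letters may be illustrative, and 2.6 does not mention them. This much stands: the contradiction is conditional on who does what. It does not clear the text, because no separate blinded operator is described and 2.7(2) states the key flatly.

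A reader might go further in three ways that the article does not support.
- **That analyst blinding does not exist.** This needs the analysis data to carry the device letters, and no section says so.
- **That clinical staff can see the allocation in the chart.** In 2.6 the envelope is still sealed when the coordinator selects it for the chart, and the experimenter opens it afterwards. Nothing says the opened envelope or its contents go back there, and 2.11.1 separately says the clinical and nursing providers are blind.
- **That the bias is a given share of the detectable MADRS difference.** The article gives no MADRS SD and no target difference, and section 2.5 uses a two-proportion formula without stating the proportions. Any such percentage would divide one assumption by another.

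**Conclusion.** The point holds in a limited form. If the experimenter is the implementer, 2.6 and 2.7 cannot both be followed, and this is so whether the envelope names the arm or a letter. If they are different people, 2.7(1) may be true, but the article does not describe the arrangement and the printed key weakens it. Analyst blinding is at risk only if the A/B labels carry through to the analysis. Blinding of participants, outcome collectors and the third-party evaluator is stated separately and is not directly removed, although 2.11 and 2.7(2) must be reconciled on who performs the assessments.

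The reach is all 240 planned participants, since one key covers both modes. The size of any resulting bias cannot be derived from the article. The text is wrong as written and should be corrected before the blinding claim is relied on.

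**What to change.** - Remove the A/B key from the protocol and have the third party already named in 2.7 hold it. Because the present key is printed, assign new codes rather than only deleting the sentence.
- Put codes in the envelopes that do not reveal the arm: participant-specific, or several per arm, if the device allows.
- State who opens the envelope, who programs the device and who gives the sessions, and use one term for each role across 2.6, 2.7 and 2.11.
- State that whoever opens the envelope or programs the device does not rate the MADRS, and reconcile the therapist-conducted assessments in 2.11 with the third-party evaluator in 2.7(2).
- Give analysts group labels unrelated to the device modes, so that the two-step unblinding in 2.7(3) has content.
- If the operator cannot be blinded, delete the claim in 2.7(1) and describe the trial as participant- and assessor-blind.

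The cost is a code list and some set-up time, using the third party already in the plan; no extra staff are needed. The change should be made before enrolment, because staff who already know a participant's arm cannot be re-blinded.
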